## Evidencing outcomes and giving them a value

### Evidencing outcomes

This stage involves finding data that demonstrates whether preferred outcomes have occurred and then valuing those outcomes. A convergent parallel mixed method approach will be employed, consisting of qualitative and quantitative data collection and analysis and then comparing and relating the two before interpreting them (34).

All participants will be asked demographic questions about their age, gender identity, cultural background, language spoken at home and the nature of their family member’s illness. They will also be asked which Satellite program/s they have been involved in.

For the quantitative component of the evaluation, a within-subject pre-post study design will be used to identify potential changes over time (35). Accordingly, participants (and their parents, for children aged 18 years and under) in targeted programs will be invited to participate in questionnaires on program entry, and then 6 months later, using the number of programs as a covariate (as some will attend multiple programs). Participants are asked to record a nickname when completing questionnaires, to ensure traceability across time one and two (pre and post). Individual and longitudinal conversations will also be employed. Further detail for these steps is presented below.

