### Measures

Measurement tools and processes were identified as per the program outcomes highlighted in the Theory of Change. In discussion with the YAC, it was determined that *belonging* referred to feelings of safety and comfort associated with particular groups of people. ***Connectedness*** was similar and referred to the quality of relationships (connections) with others, especially peers. It was on this basis that the Strengths and Difficulties Questionnaire [SDQ; (36)] was used as it provides a measure of ***prosocial behaviour*** (1 subscale, 5 items) in children, adolescents and young adults. The SDQ can be administered to parents or to the young person themselves if they are aged 11 years or over. Each item is answered based on a 3-point Likert scale (not true, somewhat true, certainly true) e.g., “I am helpful if someone is hurt, upset, or feeling ill.” Scores range from 0 to 10, with higher scores indicative of greater prosocial behaviour. The SDQ prosocial subscale has fair internal consistency (*α* = 0.75) and strong test–retest reliability over 12 months (*r* = 0.64; 66). Further, the SDQ subscales have age and gender norms specific to each country (including Australia), so that scores from the sample of interest can be compared with the same population from which they were drawn. The prosocial behaviour subscale will be used to measure ***connectedness*** as it examines the young person’s ability to relate well with peers. The Longitudinal Study of Australian Children (LSAC) items that pertain to connectedness will also be used to evidence this outcome (see below discussion on deadweight for an overview of the LSAC study).

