### Deadweight and displacement

Deadweight identifies changes in participant circumstances or resources that might have occurred regardless of whether the program or activity had taken place. One of ways we will calculate deadweight, is be using data from the Longitudinal Study of Australian Children (LSAC) survey, as a benchmark or comparison group of young people not involved in Satellite’s programs. The LSAC includes a group of Australian children/adolescents who have self-identified as having caring responsibilities (56). These will be matched with some of the young people who have participated in Satellite’s programs on demographic variables of age, gender and socio-economic status. Commencing in 2003, the LSAC is a national longitudinal study of data collected every 2 years on various child, parental and family characteristics that influence children’s development at different ages (56). Specific LSAC items will be used, as pertaining to connectedness /belonging outcomes, though noting that comparative data are only available for young people aged 14 years and above. This means that only some of the Satellite group will be included, and only on the connectedness outcome, with children under 13 years of age not being compared to the LSAC group and other outcomes not being compared. It is possible that one or more young people from the LSAC cohort may have attended a Satellite program. Given that Satellite is a unique program only available to young carers living in Victoria (while LSAC is an Australian cohort), and the level of help-seeking within this cohort will be variable (collected as frequency data, not details of programs), the likelihood is considered small within the Victorian LSAC participants and unlikely for those residing interstate.

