## Limitations

A potential limitation inherent in any SROI study is the monetisation of outcomes (28) and a lack of a universal bank of indicators (59). However, even those things with a market value are valued subjectively based on market conditions and consumer preferences. It was challenging to identify financial proxies for the various outcomes in this study, especially in relation to resilience as it comprised of multiple factors. As pointed out by Mook et al. (60), the choice of financial proxies can become subjective, which can compromise the reliability of the SROI. Given these challenges, Nicholls et al. (26) highlighted the importance of being transparent about the development and identification of these proxies which this protocol aims to do. Nonetheless, we agree with the notion purported by Arvidson et al. [(23), p. 233] when they argued that excluding significant outcomes which may be challenging to place a monetary value on, would “render the analysis precisely wrong, rather than the desirable “roughly right” and would greatly diminish the perceived social value of a given program.

We acknowledge the relatively short-term nature of the study and our subsequent inability to track long term change (or lack thereof). The study would have been strengthened had we been able to locate a comparison group for children under 14 years of age and for other outcomes besides connectedness. Using a currency converter to update the 2007 value of friendships presents a limitation in our analysis and may not fully capture more nuanced economic changes over time. We also acknowledge that the decision to aggregate the number of programs without employing a weighting system may limit the analysis. Similarly, the various programs offered by Satellite are delivered by different facilitators. As the knowledge, experience, skill and interpersonal style of group facilitators can have a significant impact on program outcomes (61), it will be difficult to determine which specific program/s are responsible for participant outcomes. Nonetheless, we are collecting fidelity logbooks to document the consistency of program delivery (30).

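### LSAC deadweight for connectedness (ages about 14 and over) is not a six-month counterfactual: the comparator is measured every two years and matched on demographics only

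*Protocol article*

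**What the plan says.** All references are to the Protocol article.

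- **Comparator.** Under Deadweight and displacement, LSAC members who identify themselves as carers serve as the benchmark for young people outside Satellite. The section states that "the LSAC is a national longitudinal study of data collected every 2 years on various child, parental and family characteristics".
- **Satellite measurement.** Under Evidencing outcomes, participants "will be invited to participate in questionnaires on program entry, and then 6 months later". Table 3 and Calculating the SROI value the outcomes over the same six months.
- **Matching.** Some Satellite participants are matched to LSAC carers "on demographic variables of age, gender and socio-economic status". Starting connectedness is not among the variables.
- **Outcome scale.** Under Measures, "The prosocial behaviour subscale will be used to measure" connectedness, and the LSAC connectedness items are used as well. Table 3 lists both sources.
- **Age.** LSAC comparison data are said to exist only from age 14. The same section then restricts the comparison "with children under 13 years of age not being compared to the LSAC group". Limitations says the study would have been stronger "had we been able to locate a comparison group for children under 14 years of age".
- **Other sources and sensitivity.** Interviews qualify the LSAC result and supply deadweight for other ages and outcomes. Each key assumption is varied by ±10% one at a time, and best-case, moderate and worst-case scenarios are added without stated ranges.

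**The concern.** Deadweight should be the change these young people would have shown over the same six months without Satellite. A two-yearly survey offers either a change over a period four times as long or a level at one wave. Neither is the quantity needed, and the article gives no bridge between them.

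The match has a separate weakness. If entrants tend to be less connected than other carers of the same age, gender and socio-economic status, part of their pre-post gain is regression to the mean. The matched carers would not show it, because they were not selected on a low starting score. That part of the gain would be credited to the programme. If LSAC supplies a level instead, the starting difference enters the comparison directly.

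The age wording leaves 13-year-olds neither excluded nor provided with comparison data.

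Connectedness carries the largest proxy in Table 3, so its deadweight percentage has leverage on the ratio wherever LSAC is the source.

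**Working it through.** **The plan's own figures.** The article states no deadweight percentage, so there is none to reproduce. Its sample size for this comparison, 29 per group, cannot be confirmed or refuted because the test and any correlation are not stated; nothing below depends on it. The connectedness proxy is used as printed, $21,861.38. Half of the printed annual figure is 42,818.76 / 2 = $21,409.38. That is a separate discrepancy and does not affect the ratios below.

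**Inputs.** LSAC interval 24 months; Satellite interval 6 months; proxies $21,861.38, $4,200 and $1,250 (Table 3). *Assumed:* a two-year LSAC change is deducted unscaled, drift is linear, and unscaled deadweight *a* is between 10% and 40%.

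**Step 1, time basis.** 24 / 6 = 4, so deadweight scaled to six months is *a*/4.

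**Step 2, net connectedness value per participant.** Net = 21,861.38 × (1 − deadweight). Understatement factor = (1 − *a*/4) / (1 − *a*).

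| Unscaled *a* | Scaled *a*/4 | Net, unscaled | Net, scaled | Factor |
|---|---|---|---|---|
| 10% | 2.5% | $19,675 | $21,315 | 1.08 |
| 20% | 5% | $17,489 | $20,768 | 1.19 |
| 40% | 10% | $13,117 | $19,675 | 1.50 |

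The factor keeps rising with *a*: at 80% it is 0.80 / 0.20 = 4.00. With the other two proxies added undiscounted (4,200 + 1,250 = 5,450), the per-person total changes by (21,315 + 5,450) / (19,675 + 5,450) = 1.07 at 10% and (19,675 + 5,450) / (13,117 + 5,450) = 1.35 at 40%.

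**Step 3, the sensitivity step.** Read as a relative change, ±10% around *a* = 40% covers 36% to 44%, or net values of $13,991 to $12,242; the scaled value is $19,675. A relative step of a tenth never reaches a four-fold difference. Read as ten percentage points, the step misses the scaled value once *a* − *a*/4 exceeds 0.10, that is, once *a* exceeds 0.10 / 0.75 = 13.3%.

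**Step 4, why scaling alone does not settle it.** Let *D* be six-month drift and *R* the regression to the mean in carers matched on low starting connectedness. As a simplification, take *R* to appear in full at the next measurement, whenever that is.

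- Needed: *D* + *R*
- Two-year change, unscaled: 4*D* + *R*
- Two-year change, scaled: *D* + *R*/4

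Quartering a baseline-matched change keeps only a quarter of the regression. When *D* and *R* have the same sign, the needed value lies between the scaled and unscaled results, so these act as bounds. When *D* is negative and *R* positive, *D* + *R* exceeds both, and they do not bracket it.

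**The case against.** The strongest reply is that this is a condensed article. It calls LSAC a benchmark and never says that a wave-to-wave change will be computed or deducted unscaled. Choice of wave, level or change, and scaling commonly sit in an analysis plan, and the larger evaluation it cites is not shown. This stands against treating the silence as an error in itself. It does not answer what the article does fix: a two-yearly comparator for a six-month estimate, a list of matching variables, and an age cut that disagrees with itself.

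Several stronger readings are tempting but unsupported:

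- **Different scales.** A reader might infer that the gain is scored on the SDQ and deadweight on LSAC items. Measures and Table 3 plan the LSAC items for Satellite participants too, so a common scale is available. What remains open is which of the two gains is valued.
- **Purely demographic comparability.** The pool is first limited to self-identified carers, and Attribution controls for earlier Satellite attendance and records other service use. None of this addresses starting connectedness. That entrants are unusually isolated is plausible but not documented.
- **80% of value at stake.** Connectedness is 21,861.38 / 27,311.38 = 80% of the summed per-person proxies. LSAC deadweight touches only participants aged about 14 and over, in programmes that start at age 8, and interviews also inform it.
- **Overvaluation if LSAC connectedness falls.** This requires negative deadweight to be applied, whereas Calculating the SROI treats deadweight as a discount.

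**Conclusion.** The point holds for connectedness in participants aged about 14 and over. As fixed in the article, the LSAC comparison is not a like-for-like six-month counterfactual: the interval is four times too long, the match leaves starting connectedness free, and the age limit is inconsistent.

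The four-fold overstatement of the deadweight percentage is conditional on an unscaled two-year change and linear drift. It would be wrong to infer that the SROI ratio itself is wrong several-fold. At 10% to 40% unscaled deadweight, net connectedness value is understated by a factor of 1.08 to 1.50, only in the group LSAC covers. If LSAC supplies a level, the four-fold factor does not arise and the baseline problem remains. The bias from matching cannot be sized from the document.

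**What to change.** 1. In participants aged 14 and above, use the LSAC connectedness items for both the gross gain and the deadweight. Keep the SDQ prosocial score as supporting evidence.
2. Add entry connectedness on those items to the matching or adjustment, alongside age, gender and socio-economic status.
3. State whether LSAC supplies a level or a change. If a change, report deadweight both unscaled and scaled to six months (one quarter) as bounds, because drift may scale with time and regression to the mean does not. State that the bounds bracket the answer only when drift and regression run in the same direction. Carry them into the sensitivity analysis in place of ±10%.
4. Use one age limit, 14 and above, in Deadweight and displacement and in Limitations.

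The cost is wording and modest extra analysis on data already planned. Some participants may have no close match on entry connectedness; adjustment avoids dropping them but relies on a model. Deadweight becomes a range rather than one figure.

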An *a priori* power analysis was conducted using G*Power version 3.1.9.7 software (65) to determine the minimum sample size required for the study. The required sample size to achieve 80% power for detecting a medium effect at a significance criterion of *α* = 0.05 will be 29 per group {intervention [Satellite participants] and usual care [LSAC]; as per (30)}. Other deadweight measures will be ascertained by asking young people what they perceive would have happened if they had not attended Satellite and their estimation of the impact of that occurrence (in the interviews). This is necessary as there is a risk that LSAC participants may be engaged in programs similar to Satellite. Their responses will be used to inform and qualify any differences between the LSAC calculations and the Satellite participant sample as well as deadweight across other age groups and for other outcome measures not included in the LSAC data set.

Displacement is an assessment of how much the outcome might have displaced other outcomes, including the occurrence of negative outcomes for the children and young people and others. An evaluation of a similar program {Paying Attention to Self [PATS]; (57)} found that building new connections with participants during the program came at the cost of building peer relationships in other sites outside the program such as school and this is a concern that could apply here. Alternatively, participants could be gaining transferrable social skills at Satellite that then lead to better connections at school and other settings. We will be investigating this and other potential outcomes in the conversations with young people and who they are turning to.

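### The stated 80% power at 29 per group cannot be reproduced for a medium Satellite-versus-LSAC difference; on the usual two-group reading (d = 0.5) it is about 46%

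*Protocol article*

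**What the plan says.** Under Deadweight and displacement, the protocol article describes an a priori G*Power calculation: "The required sample size to achieve 80% power for detecting a medium effect at a significance criterion of" α = 0.05 is "29 per group {intervention [Satellite participants] and usual care [LSAC]; as per (30"). The last item refers to the larger evaluation of which the SROI is part. The effect has a label but no metric or value. The test, sidedness, number of measurements and within-person correlation are not given.

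The same section matches LSAC young carers to some Satellite participants on age, gender and socio-economic status. LSAC data are collected every 2 years, and the comparable items exist only from age 14: "This means that only some of the Satellite group will be included, and only on the connectedness outcome". Evidencing outcomes plans Satellite questionnaires at entry and 6 months. Data analysis names repeated-measures MANCOVA, without tying it to the LSAC comparison.

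**The concern.** The sentence names two groups, a power, an alpha and an effect label, so a reader will take it as a two-group comparison of a conventional medium difference. On that reading 29 per group is less than half of what is needed.

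LSAC is the only external comparison for deadweight. The other source is what participants say in interviews would have happened without Satellite. The outcome it serves, connectedness, carries most of the money in Table 3: with the values as printed, 21,861.38 / (21,861.38 + 4,200 + 1,250) = 21,861.38 / 27,311.38 = 80%. An imprecise LSAC contrast therefore passes into the SROI ratio, while the stated 80% suggests that precision is adequate. The planned one-at-a-time ±10% variation in Calculating the SROI is not tied to the sampling error of the deadweight estimate.

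**Working it through.** **Inputs.** From the article: α = 0.05, power 80%, two groups of n = 29. Assumed, because not stated: medium means d = 0.5 (f = 0.25 for two groups), two-sided unless noted, unit SD.

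**1. Trying to reproduce 29 with two independent groups.** The noncentrality is d√(n/2) = 0.5 × √(29/2) = 1.904, on 56 degrees of freedom, with two-sided critical value 2.003.
- Power at 29 per group: 46.5% two-sided, 59.3% one-sided.
- Needed for 80%: 64 per group two-sided (63 gives 79.5%, 64 gives 80.1%); 51 one-sided.
- Detectable at 80% power with 29 per group: d = 0.75 two-sided.

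The printed 29 is not reproduced.

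**2. Allowing for matching.** Paired t-test with d = 0.5 on the pair difference, noncentrality 0.5 × √29: 73.9% two-sided at 29 pairs (34 needed), 83.7% one-sided (27 needed).

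**3. Allowing for baseline adjustment (ANCOVA).** The effective effect is d/√(1 − r²).

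| assumed r | effective d | power at 29 per group | n per group for 80% |
|---|---|---|---|
| 0.5 | 0.577 | 58.0% | 49 |
| 0.75 | 0.756 | 80.8% | 29 |

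ANCOVA gives 29 only with r near 0.75.

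**4. The G*Power group-by-time interaction.** Two groups, two measurements, f = 0.25, N = 58: λ = f² × N × 2/(1 − ρ).
- ρ = 0.1: λ = 0.0625 × 58 × 2/0.9 = 8.06, power 79.7% (60 in total, 30 per group, for 80%).
- ρ = 0.15: 81.9%.
- ρ = 0.5: λ = 14.5, power 96.3% (17 per group would do).

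So this route reaches 80% at about 29 per group. But f = 0.25 for a 2 × 2 interaction means cell effects of ±0.25 SD, and so a difference in change of 4 × 0.25 = 1.0 SD. As a check, a t-test on change scores with a 1.0 SD difference has standardised effect 1/√(2(1 − ρ)) = 0.745 at ρ = 0.1, and 29 per group gives 79.7%, the same figure.

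For a 0.5 SD difference in change, the standardised effect is 0.5/√(2(1 − ρ)):

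| ρ | standardised effect | power at 29 per group |
|---|---|---|
| 0.1 | 0.373 | 29% |
| 0.5 | 0.500 | 46% |
| 0.64 | 0.589 | 60% |

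**5. Another route near 29.** Regression with f² = 0.15 and one tested coefficient needs 55 in total, about 28 per group. The article does not state that metric.

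**6. Precision.** For an unadjusted difference at 29 against 29, the 95% CI half-width is 2.003 × √(2/29) = 0.53 SD, slightly wider than the medium effect itself.

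**The case against.** The best defence is that no t-test is mentioned. The article describes a pre-post design and a repeated-measures model, and in G*Power's interaction convention 29 per group is enough at ρ of about 0.1 and more than enough above it. The calculation is also referred to the larger evaluation, and a condensed article may leave the test and correlation there. Both points stand to this extent: a reader might infer that the true power is 46%, and the document does not support that without conditions. The power depends on a test that is not named.

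The defence does not rescue the printed sentence. The interaction route calls a full-SD difference in change medium. It also needs pre and post values on the same footing in both groups, and two-yearly LSAC waves are not shown to give them against a 6-month Satellite interval.

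Three other tempting readings should be set aside.
- The 0.64 in Measures is a 12-month retest value for the SDQ prosocial subscale. It cannot be taken as the correlation for the LSAC connectedness items, for which none is given.
- LSAC is external, but nothing shows that it is free of self-report; its carers are self-identified.
- The article does not say that deadweight turns on a significance test. LSAC is one of several sources, with interviews used to qualify it, and 29 is described as a minimum. The weakness is imprecision, not a stated decision rule.

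**Conclusion.** The point holds in conditional form. If the Satellite–LSAC comparison is a difference between two groups and medium means d = 0.5, then "will be 29 per group" gives 46% power two-sided, and between 58% and 74% under the more favourable two-sided set-ups of baseline adjustment at r = 0.5 or matched pairs. The requirement for the simple comparison is 64 per group, and 29 supports d of about 0.75. The routes that come close to 29 need unstated inputs: ANCOVA at r near 0.75, an interaction with ρ near 0.1, a one-sided paired test, or f² = 0.15. The article links none of them to the LSAC contrast. The power statement is therefore unreproducible as printed, and it fails on its natural reading.

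**What to change.** Restate the power claim for the Satellite–LSAC comparison that will actually be made, giving the test, effect metric, sidedness and assumed correlation. For example, for a two-sided comparison of two independent groups, 29 against 29 has 80% power for d of about 0.75 and about 46% for d = 0.5. If an interaction was intended, say that f = 0.25 is a 1.0 SD difference in change and show that LSAC can supply matching pre and post values.

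Report the LSAC-based deadweight as an estimate with a 95% CI, and use the limits of that interval in the SROI sensitivity analysis alongside the ±10% changes.

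Where enough eligible LSAC carers exist, use more than one comparator per Satellite participant. The records already exist, but the gain depends on how many carers are available and on a usable baseline. The article gives neither, so no particular power should be promised.

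The cost is wording, a less favourable stated power, and a little more analysis.
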